## Methods: evaluation

### Quantitative data (adherence to ANC package and early initiation of ANC)

The primary outcomes or indicators of interest, which will be measured to assess the impact of the adapted ANC packages, vary across each country (see Table 2). These measures are based on the WHO ANC monitoring framework [29].

**Table 2 Tab2:** Primary outcomes by country

	Burkina Faso	India	Rwanda	Zambia
Syphilis testing at first ANC contact	X	X	X	X
First ANC contact within 12 weeks	X	X	X	X
Iron and folic acid (IFA) supplementation received for 90+ days	X			
Haemoglobin (Hb) screened at first ANC contact		X	X	X
Total number of ANC contacts	X	X		
Blood pressure measurement at first ANC contact				X

X denotes which primary outcomes are being tracked in each country

Data collection for the stepped-wedge cluster randomized trial will be cross-sectional every month. Country teams will leverage existing data collection systems to gather data on primary outcomes. Specifically, teams will use ANC registers at the health facility and client cards/patient files as primary data sources. They will also collect information on cases referred to a higher level of treatment (e.g. district health hospital) for further management, where available. Secondary outcomes or indicators of interest (see Table 3) vary across each country.

**Table 3 Tab3:** Qualitative methods and stakeholder groups by country

	Burkina Faso	India	Rwanda	Zambia
Pregnant women who seek ANC at selected facilities or within the selected facilities’ catchment areas	IDIs and FGDs	IDIs	FGDs	FGDs
Husbands/partners or mothers-in-law (household decision maker) from the selected catchment areas	IDIs	IDIs	FGDs	
Selected community leaders and/or champions for maternal health	IDIs			FGDs
Community health workers rendering services within catchment area of selected health facilities	IDIs and FGDs	FGDs		
Health workers providing ANC services at selected facilities or within catchment area of the selected facilities	IDIs	FGDs	FGDs* & IDIs	FGDs* & IDIs
Health facility managers of selected facilities		IDIs	IDIs	IDIs
Government health officials/program managers responsible for maternal health programs at district/state or national level	IDIs	IDIs	IDIs	

*IDIs* in-depth interviews, *FGDs* focus group discussion

*FGDs with health workers using the digital tool during the formative phase

Additional outcomes will be measured using data collected through exit interviews (Rwanda and Zambia) and nested cohort study interviews (India and Burkina Faso) with pregnant women. This component will aim to assess the quality of ANC service provision (receipt of recommended evidence-based services), acceptability, and experience of care. To recruit women, health workers may conduct the first selection of potential participants while the country team will then follow up and gather informed consent. Health workers will not receive any remuneration for taking part in the study; therefore, they do not have an incentive to recruit participants. During the consent procedure it will be clearly explained to the women that participation is voluntary, and that their care will not be affected by their decision.

### Qualitative data (acceptability of the ANC package)

To understand whether the adapted ANC packages are acceptable to and create value for women and health workers as well as their experience of care, we will collect and analyse qualitative data. Qualitative components will entail in-depth interviews (IDIs) and focus group discussions (FGDs) with purposively identified participants from stakeholder groups. Questions for the FGDs and the IDIs have been developed on the basis of the theoretical framework of acceptability to gauge women’s and health workers’ affective attitude and perceived effectiveness towards the adapted ANC package as well as their understanding (intervention coherence) of it and the sense of self-efficacy when delivering the package [21]. The stakeholder groups (see Table 4) . Additionally, qualitative data will explore the potential conditions for sustainability and scale up.

Country teams will conduct facility assessments at all the study sites using a standard process evaluation form for monitoring. The evaluation form will include items for measuring the readiness of study facilities in terms of supplies and equipment, in addition to training and supervision needs. The implementation of the updated adapted ANC package will be further documented to understand to what extent the co-interventions were performed as intended and factors that inhibited or promoted effectiveness, allowing for iteration where necessary, using the adapted version of WHO Programme Reporting Standards [30]. The analysis of these data will measure the extent of fidelity to the implementation strategy and explore its association with study outcomes.

Costing data will also be gathered during the cohort study exit interviews with pregnant women. The cost per contact will be estimated through exit interviews with beneficiaries as part of the main evaluation. Direct costs are anticipated to include all out-of-pocket costs incurred in seeking ANC, including consultation fees, transportation costs, medicine and other supply costs. Indirect costs will additionally be assessed, including wages lost and childcare costs as a result of time spent seeking ANC. Additionally, economic costs incurred by implementing partners will be tracked prospectively.

To determine the full spectrum of costs to the health system, a range of methods will be employed, including (1) tracking marginal commodity costs (through implementation research partners and WHO program records); (2) understanding infrastructure costs, including buildings and capital equipment; and, in Burkina Faso and India only, (3) assessing health worker's time.

To support the measurement of health worker time, teams will conduct observations of health worker's efforts during ANC service delivery, followed by IDIs with the health workers observed. Observations and interviews will be done at two time points in the same geography: (1) prior to guideline introduction (baseline) and (2) once the revised guidelines have been introduced and the program stabilized. Data collection will be carried out by implementation research staff using (a) structured observation sheet per type of ANC patient observed and (b) an IDI guide. The latter will be implemented as part of IDIs with health workers, who were observed and seek to understand their perceptions of time allocation on the basis of different ANC contacts and patient risk profiles. A total of 480 observations will be conducted during the baseline period and 480 observations during the intervention period across both states. All pregnant women receiving ANC services on the day of observations will be eligible to be observed. For the observations, verbal consent will be obtained from the health worker and pregnant women.

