Since February 2018, the governments of Burkina Faso, Rwanda and Zambia, as well as Assam and Tamil Nadu states in India, have prioritized the adaptation and adoption of the WHO ANC recommendations. Initial efforts lead to the development of the WHO ANC recommendations adaptation toolkit [19]. Governments and stakeholders employed the toolkit to adapt the ANC package and update national- and state-level ANC policies. As a next step, this protocol outlines implementation research, applying the Capability Opportunity Motivation-Behaviour (COM-B) model for behaviour change to design co-interventions, and the theoretical framework of acceptability, to better understand what it will take to provide quality, integrated and person-centred ANC packages [20, 21]. In Rwanda and Zambia, this will include the deployment of a country-adapted digital intervention (WHO digital ANC module) to support the implementation of their ANC packages [22], in line with national digital health strategies [23] and the WHO’s SMART guideline approach [24].

In collaboration with Ministries of Health (MoHs) and country research partners, the study uses implementation science to systematically introduce and test the applicability of the adapted ANC package in selected sites across four countries. It aims to generate key evidence on the implementation of the adapted ANC packages and inform future national adaptation and scale up. Study objectives are outlined in Table 1; in Rwanda and Zambia, there will be a formative phase.

**Table 1 Tab1:** Study objectives

Burkina Faso and India
*Primary objectives*
1. Does the adherence to the country/state package of ANC interventions by health workers improve with the country/state-specific ANC package? a. Does the implementation of country/state-specific ANC package (including targeted community mobilization) increase early initiation of ANC among pregnant women? 2. Is the country/state-specific ANC package acceptable to and does it create value for women and health workers?
*Secondary objectives*
1. What are the human resources training and supervision needs of implementing the country/state-specific ANC package? 2. What is the cost of implementing the country/state-specific ANC packages compared with standard of care? 3. What are the effects of the ANC package on retaining women in ANC services? (Burkina Faso only)

Rwanda and Zambia
*Formative phase*

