### Logic model

A logic model was developed to specify the components of the co-interventions and how they are proposed or hypothesized to bring about changes in ANC service delivery (including improving implementation of the adapted ANC package) and uptake. We drew on the COM-B model of behaviour change and the related, Behavior Change Wheel, employed to conceptualize and describe the behaviour change targeted by the co-interventions [20]. COM-B proposes three necessary conditions for a desired behaviour to occur: (1) the person’s psychological and physical ability to perform it (capability – that is, having the necessary knowledge and skills), (2) their reflective and automatic mechanisms which ‘energize’ or prevent it (motivation – that is, strong intention to perform the behaviour, perceived importance, priority, advantages and disadvantages) and (3) the external social and environmental opportunity which enables or inhibits it (opportunity – that is, available resources, team culture and working norms) [20].

Each co-intervention addresses one of these conditions. Training health workers will build health workers’ capability through increasing knowledge, skills, and understanding of the adapted ANC package. Providing the necessary supplies and equipment will reduce barriers and increase health workers’ opportunity (physical) to implement the ANC package. In Rwanda and Zambia, employing the country-adapted digital module will support health workers’ capability, enabling them to adhere to the provision of the ANC package. Mentoring and supervision will provide hands on learning opportunities (social) and examples to imitate, as well as increase motivation through persuasion. Community mobilization will impact social influences on women, their families and key community stakeholders through persuasive communication. Better trained and supported health workers and available supplies aim to increase the positive experiences and perceptions that women have of ANC services, increasing their demand. Additionally, community-level messaging will focus on the importance of ANC seek to influence and encourage women and their families to access ANC early and more frequently. Figure 1 outlines and categorizes the four study co-interventions, linking them to the relevant COM-B domain and study outcomes.

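### In Burkina Faso and India the only summary named for women's costs is cost per contact, although the package aims to raise the number of contacts; cost per pregnancy should carry the comparison.

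*Protocol article*

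**What the plan says.** Costing is described under Methods: evaluation, in the section Qualitative data (acceptability of the ANC package). It says "Costing data will also be gathered during the cohort study exit interviews with pregnant women" and then "The cost per contact will be estimated through exit interviews with beneficiaries as part of the main evaluation". The components follow: "Direct costs are anticipated to include all out-of-pocket costs incurred in seeking ANC" (fees, transport, medicines, supplies), and indirect costs "including wages lost and childcare costs as a result of time spent seeking ANC". No cost per woman or per pregnancy is named anywhere in the article. Costs to implementing partners and to the health system are tracked separately in the same section.

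For Burkina Faso and India, Table 1 (Study objectives) lists as a secondary objective: "What is the cost of implementing the country/state-specific ANC packages compared with standard of care". For Burkina Faso alone it adds: "What are the effects of the ANC package on retaining women in ANC services". Table 2 marks "Total number of ANC contacts" as a primary outcome in these two countries. The Logic model section says community messaging will "encourage women and their families to access ANC early and more frequently". Under Study design – India & Burkina Faso, cohort women are followed to the end of pregnancy, one cohort under control conditions and one under the intervention.

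**The concern.** A unit cost compares two conditions fairly when the number of units per person is the same in both. Here the unit is the contact, and the package is designed to raise the number of contacts per woman. Transport, lost wages and childcare recur with each attendance, so a woman who attends more often bears more of them. A mean cost per contact does not show that increase.

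One-off costs in a pregnancy add to the problem. Spread over more contacts, they lower the per-contact mean although nobody has saved anything.

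The more the package succeeds on its own primary outcome, the more a per-contact figure, read alone, understates the change in what a pregnancy costs the woman. The study is meant to inform national scale-up, so the women's side of the cost comparison should be able to show this.

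**Working it through.** The article states no cost figure, no expected number of contacts and no sample size for costing, so there is no figure to reproduce. The check is an identity with assumed inputs.

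**Inputs from the article:** women's costs are estimated per contact (costing text); the cost objective is comparative (Table 1); number of contacts is a primary outcome in Burkina Faso and India (Table 2); more frequent attendance is intended (Logic model); the cohort is followed to the end of pregnancy (Study design – India & Burkina Faso).

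**Assumed inputs:** all contact numbers and cost units below.

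**Identity.** Mean cost per pregnancy = mean contacts × contact-weighted mean cost per contact. Hence

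per-pregnancy ratio = (per-contact ratio) × (contacts ratio),

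and cost per pregnancy falls only if the per-contact ratio is below (control contacts ÷ intervention contacts).

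**Modest case.** With unchanged cost per contact, 10% more contacts gives 1.00 × 1.10 = 1.10 (+10%), and 25% more gives 1.00 × 1.25 = 1.25 (+25%). In both, a per-contact comparison shows 0%.

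**Wider range of assumed contacts:**

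| Contacts, control to intervention | Per pregnancy, cost per contact unchanged | Per pregnancy, cost per contact 10% lower | Fall in cost per contact needed to break even |
|---|---|---|---|
| 4 to 5 | +25% | 0.9 × 1.25 = 1.125 (+12.5%) | 1 − 4/5 = 20% |
| 6 to 8 | +33% | 0.9 × 1.333 = 1.20 (+20%) | 1 − 6/8 = 25% |
| 4 to 6 | +50% | 0.9 × 1.5 = 1.35 (+35%) | 1 − 4/6 = 33% |
| 4 to 8 | +100% | 0.9 × 2 = 1.80 (+80%) | 1 − 4/8 = 50% |

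**Opposite signs.** Let a pregnancy have a one-off cost F and a recurring cost a per contact, with k contacts. Cost per contact is F/k + a, which falls as k rises. Cost per pregnancy is F + a·k, which rises. With F = 4 and a = 1:

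- 4 to 5 contacts: per contact 4/4 + 1 = 2.0 to 4/5 + 1 = 1.8 (−10%); per pregnancy 4 + 4 = 8 to 4 + 5 = 9 (+12.5%).
- 4 to 8 contacts: per contact 2.0 to 4/8 + 1 = 1.5 (−25%); per pregnancy 8 to 4 + 8 = 12 (+50%).

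So an apparent saving per contact can accompany a higher cost per pregnancy with no change in any underlying price.

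**The case against.** The strongest reply is that the criticised comparison is not in the text. The article names cost per contact as a quantity to estimate. It does not say that the two conditions will be compared on it, or that it is the only or final metric. Unit cost times quantity is an ordinary way to build a total, the quantity here is itself a primary outcome, and a rise in contacts would be reported anyway. An article may leave the aggregation to a fuller costing or analysis plan. This stands, and it sets the strength of the point. A reader might infer that the study plans a per-contact comparison and will therefore report a misleading result; the document does not support that.

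Second, the objective speaks of the cost of implementing the package, which points first to partner and health-system costs, and these are tracked separately. This also stands. A reader might infer that the whole cost evaluation is compromised, or that ministries will decide on women's cost per contact. The article says neither.

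Third, all sizes are assumed. A doubling of contacts would be an extreme reading. Cohort women are recruited at a first contact in the first trimester, so the cohort may not show contacts gained through earlier initiation. The modest range is the safer illustration.

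Fourth, the scope is not all four countries. In Rwanda and Zambia the number of contacts is not a primary outcome, and the cost objective asks what resources are needed, with no comparison with standard care.

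What the reply does not remove is that the one unit the article states for women's costs cannot, alone, answer a comparison between conditions when the number of contacts is expected to differ.

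**Conclusion.** The point holds in limited form. For women's direct and indirect costs in Burkina Faso and India, the only named summary has a denominator that the package is meant to change. Used alone, it could show no change or a fall while women's cost per pregnancy rises. The direction follows from the identity. The size cannot be taken from the document: with assumed increases of 10–25% in contacts and unchanged cost per contact, cost per pregnancy is 10–25% higher. It would be lower than under standard care only if cost per contact fell by more than 1 − 1/1.10 = 9% or 1 − 1/1.25 = 20% respectively. The point does not touch the partner or health-system costs or the effectiveness outcomes. It is worth acting on because a better unit is available at almost no cost.

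**What to change.** State in the costing text that, for the nested cohort in Burkina Faso and India, women's cost per pregnancy is the measure compared between conditions. Where cost is recorded at every contact, sum it over the woman's contacts. Otherwise multiply her cost per contact by her own number of contacts. Do this woman by woman: the product of two group means equals the mean cost per pregnancy only if the cost mean is weighted by contacts. Report cost per contact and number of contacts beside it, so that readers can see which part moved.

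The cost is about one sentence and no design change, since the cohort is followed to the end of pregnancy and contacts are already an outcome. There are two small downsides. The article does not say that cost is asked at every contact; if it is not, the total assumes that the contacts with cost data represent the others, and this should be stated. Also, the India cohort sample size allows for women moving to the private sector, so the plan should say how their later contacts and costs are handled.

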### Study population and sample size

For the stepped-wedge cluster randomized trial, data will be collected cross-sectionally from facility ANC registers (modified for this study). To ensure data quality across health facilities, an orientation for improving quality or recording and reporting will be organized across all study sites at the beginning of the study.

For the nested cohort component of the study, the pregnant women who seek ANC for the first time at the selected health facilities or at public health platforms within their catchment area will be approached and invited to participate in the study. The cohort recruitment will be closely monitored and mitigation efforts, such as additional recruitment and extension of enrolment time to ensure that the sample size is not negatively impacted, will be employed.

#### For stepped-wedge cluster randomized trial (India)

For estimating the sample size for the stepped-wedge cluster randomized design, we utilized one of the primary indicators: proportion of pregnant women who were screened for syphilis during their pregnancy. The current estimates for this indicator are approximately 20% in both Tamil Nadu and Assam. Considering 20% as the baseline, and our study having 80% power to detect a minimum change of 15%, alpha error of 5%, cluster size of 100 per period, intracluster correlation coefficient (ICC) of 0.1 and cluster autocorrelation coefficient (CAC) of 0.8, the total sample size computed is 4800 women, or 800 per period. To account for issues around data loss (incomplete entries, errors in entries, etc.), we have further inflated this computed sample size by 20%. This results in a total sample of 5760 women, or 960 per period.

#### For nested longitudinal data collection (India)

For estimating the sample size for the nested longitudinal study, the research team considered a secondary outcome indicator, that is, proportion of pregnant women whose blood pressure, weight and Hb are checked at least once in each trimester. As there are no reliable estimates for this indicator from either Tamil Nadu or Assam, we assumed it is approximately 50%. For our study to detect the relative risk within 20% of true value, which we assumed to be 1.25 (*P*1 = 62.5%), the computed sample size is 124. To account for clustering by health facility, we considered a design effect of 1.5, which leads to a sample size of 186. To account for loss to follow-up and the probability of some participants shifting to the private sector during the course of their pregnancy, we further inflated the sample by 25%, which leads to a sample size of 233. The country team rounded it up to 240 to equally distribute the sample across four health facilities of each arm (60 per health facility). Therefore, we will follow a total of 480 pregnant women, 240 during three consecutive non-intervention periods and 240 during three consecutive intervention periods through their pregnancy.

#### For nested longitudinal data collection (Burkina Faso)

To estimate the sample size for the nested longitudinal study, we considered that only 81.7% of pregnant women attended at least one ANC contact [31]. The research team will consider an improvement of 10% with the intervention, that is, *P*1 = 91.4% and exposed/unexposed ratio = 1. The team considered a level of confidence of 95% and a power of 80%. The calculated sample size is 400. Considering the grouping by health facility, we considered a cluster effect of 1.5, which leads to a sample of 600. Accounting for the loss to follow-up of certain women, the country team further increased the sample by 10%, which leads to a sample size of 660 women (330 in each arm). The first 44 pregnant women who will come to each selected health facility for ANC after the start of the enrolment phase will be approached and invited to participate in the study.

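### The Burkina Faso cohort is sized on having at least one ANC contact, which every woman has met on entry, so the stated 80% power applies to no outcome the cohort can measure

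*Protocol article*

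**What the plan says.** The protocol article, under the nested longitudinal data collection heading for Burkina Faso, gives the planning outcome and its comparison rate: "we considered that only 81.7% of pregnant women attended at least one ANC contact". It continues "The research team will consider an improvement of 10% with the intervention" and sets the intervention rate and allocation at "91.4% and exposed/unexposed ratio = 1", with 95% confidence and 80% power. Then "The calculated sample size is 400"; next, "we considered a cluster effect of 1.5, which leads to a sample of 600"; a further 10% for loss to follow-up gives 660, or 330 per arm.

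The same paragraph fixes how women enter: "The first 44 pregnant women who will come to each selected health facility for ANC" once enrolment opens are approached. The section on study population and sample size describes the nested cohort in both countries as "the pregnant women who seek ANC for the first time at the selected health facilities", or at public platforms in the catchment area. The design section for India and Burkina Faso, and Table 5, likewise describe women at their first ANC contact in the first trimester. Nowhere does the article describe recruiting pregnant women who have not sought ANC.

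**The concern.** The 81.7% is a rate among all pregnant women, including those who never attend. The cohort contains attenders only. Having one contact is a condition of entry, so it cannot distinguish a cohort followed before the intervention from one followed after it.

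Two features of the article point the same way. The sample is enlarged for loss to follow-up, although an outcome already met at enrolment cannot be lost later. And the India cohort is sized on blood pressure, weight and haemoglobin being checked in every trimester, which can vary after enrolment.

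What is at stake is the only sample-size justification given for this cohort. The evaluation section assigns the cohort interviews to quality of service provision, acceptability and experience of care. None of these has a power basis for Burkina Faso. A reader who takes the 80% at face value would give a null cohort result more weight than the plan supports.

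**Working it through.** **Inputs** (all from the Burkina Faso cohort paragraph): comparison rate 0.817; intervention rate 0.914; 1:1 allocation; 95% confidence, taken as two-sided alpha 0.05; power 80%; base size 400; cluster effect 1.5; loss 10%; final size 660.

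**1. The plan's own figure.** For two proportions with pooled variance under the null,

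n per arm = [1.96·√(2·p̄·(1−p̄)) + 0.84·√(p1(1−p1) + p2(1−p2))]² / (p2−p1)²

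- 0.817 versus 0.914: p̄ = 0.8655, difference 0.097. n = 193.03, rounded up to 194 per arm, 388 in total. With continuity correction: 214 per arm, 428 in total.
- 0.817 versus 0.917: p̄ = 0.867, difference 0.100. n = 180 per arm. With continuity correction: 199.3, rounded up to 200 per arm, 400 in total.

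The printed rates come within 3% of 400, and 91.7% with continuity correction gives it exactly. Then 400 × 1.5 = 600 and 600 × 1.1 = 660. With 200 per arm, nominal power at 0.914 is 81.4%. The arithmetic is not the fault.

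**2. The printed intervention rate.** 81.7% + 10 points = 91.7%. 81.7% × 1.10 = 89.9%. Neither is 91.4%. Since 91.7% reproduces 400, a misprint is likely.

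**3. The sizing outcome under the enrolment rule.** Every description of enrolment requires a woman to be coming for ANC. Whether that is her first visit or any visit, she then has at least one contact. The proportion is 1 in each arm, the difference is 1 − 1 = 0, the variance 1 × (1 − 1) = 0, and no test of this outcome can be formed.

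**4. Is it a planned outcome?** Table 2 lists for Burkina Faso syphilis testing at first contact, first contact within 12 weeks, iron and folic acid for 90 or more days, and total number of contacts. Table 4 adds ultrasound, haemoglobin check, blood pressure and weight checks, at least three IPTp doses, and treatment started for diagnosed infections or gestational diabetes. Having one or more contacts is in neither table.

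**5. What 330 per arm could offer (illustration; the rates are assumed).** Removing the plan's loss allowance: 330 / 1.1 = 300 evaluable per arm. Dividing by the cluster effect: 300 / 1.5 = 200 effective per arm. For an outcome near 50%, which has the largest variance, the detectable difference at 80% power is

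2.80 × √(2 × 0.5 × 0.5 / 200) = 2.80 × 0.05 = 0.14, about 14 points.

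Keeping the planned difference of 9.7 points (91.4 − 81.7) and varying the comparison rate, with 200 effective per arm:

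| Assumed comparison rate | Power |
|---|---|
| 30% | 53% |
| 40% | 50% |
| 50% | 50% |
| 60% | 53% |
| 70% | 61% |
| 81.7% (the plan's) | 81% |

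The 80% therefore depends on a comparison rate as high as the plan's. It does not carry over to an outcome with a rate in the middle of the range.

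**The case against.** **The article never plans to analyse this outcome.** It appears only as a planning proportion, so a failed test of it harms no stated analysis. This stands, and it limits the conclusion. A reader might infer that the cohort's real power is nil. The documents do not support that: power for the cohort's actual outcomes is not established, which is different from zero.

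**660 may be enough.** This also stands. A reader might infer that the cohort is too small, but the article gives no baseline rate for any other Burkina Faso cohort outcome, so adequacy cannot be judged either way. It would also be tempting to borrow the ICC of 0.1 from the Burkina Faso stepped-wedge calculation and report a much larger detectable difference. That ICC is stated for another outcome (first contact before 12 weeks) and another sample; the cohort paragraph states its own cluster effect of 1.5.

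**The cohort's purpose.** A reader might take retention or number of contacts as what this cohort is there to answer. Retention is a Burkina Faso secondary objective, but no section ties it to the cohort, and primary-outcome data come from registers and client cards.

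**A slip in the wording.** At least one may be a misprint for a higher count. Nothing in the text says so, and the background section also reports that more than 80% of women receive at least one visit, so the literal reading is plausible. If it is a misprint, the paragraph still needs correcting.

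**The stepped-wedge trial is untouched.** True: its Burkina Faso sample is sized separately.

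**Conclusion.** Wrong as written. The sizing outcome of the Burkina Faso cohort is a condition of entry, met by all women in both arms and absent from the listed Burkina Faso outcomes. The 80% power therefore applies to nothing this cohort can measure. This rests only on the article's own enrolment descriptions, which agree with one another.

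The size of the consequence cannot be fixed from the document. The figure of about 14 points assumes a 50% rate, 300 evaluable women per arm and a cluster effect of 1.5. The range of 50% to 61% power assumes comparison rates of 30% to 70% and a 9.7-point difference. Neither shows that 660 is inadequate for an outcome the sponsor has yet to name.

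The misstated 91.4% is a minor inconsistency. It does not alter the planned number of women and adds little weight.

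**What to change.** 1. Remove attendance at one or more contacts as the basis for the Burkina Faso cohort.
2. Name a cohort outcome that can vary after enrolment. Candidates already in the article are blood pressure and weight checked in each trimester, at least three IPTp doses, or retention under Burkina Faso secondary objective 3. The choice is the sponsor's; if retention is chosen, say that the cohort is what measures it.
3. Keep 660 women. Give the assumed comparison rate with its source or a range, and state the power or detectable difference for 330 per arm after the stated cluster effect of 1.5 and 10% loss.
4. If any 10% improvement is retained, say whether it is absolute or relative and print the matching rate. On the present 81.7% these would be 91.7% and 89.9%.

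The cost is one paragraph rewritten and one calculation redone. No extra women are needed. The restated power or detectable effect may be less favourable than the present text suggests.
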